### Stratum B

2.8

This stratum includes patients without neurological worsening during the concerned imaging diagnosis of RN (asymptomatic RN). Based on the available literature and institutional experience, in this group, approximately 30% of patients continue to be neurologically/radiologically stable or show regression of imaging findings without the need for further interventions (including corticosteroids) in the short term [19, 20, 21]. In the proposed study with the use of CHL, 45% of patients are assumed to remain clinically and neurologically stable. With a α of 0.1 and a power of 80%, 48 patients will be needed to achieve the desired outcome. In the first stage, 23 patients will be needed for assessment and will continue to stage 2 if > 6 responses are seen. The phase 2 study will be considered successful if > 18 responses are achieved using the pre‐specified response assessment criteria. Further considering an attrition rate of 10% from lack of follow‐up and another 10% for disease progression, an estimated 58 patients will be accrued in stratum B with the purpose of achieving 48 patients with endpoints available for analysis.

### Statistical Analysis

2.9

Response rates will be analyzed using descriptive statistics. The influence of patient, disease, and treatment‐related factors on the response (binary outcomes) will be analyzed using Pearson Chi‐square or Fisher's exact test as appropriate. Survival analysis will be done using the Kaplan–Meier product‐limit method, considering the date of study accrual as the baseline. Univariate and multivariate analyses will be done using the log‐rank test and Cox regression, respectively. For exploratory analysis, the biomarkers will be compared using the t‐test and ANOVA, as appropriate. A *p*‐value of < 0.05 will be considered statistically significant. All data collection and analysis will be done using International Business Machines, Statistical Package for the Social Sciences (IBM SPSS) version 29.

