### Stratum A

2.7

The response rate at 1 month with a combination of steroids and CHL in this study is expected to be 65% as compared to the standard 50% response with the use of dexamethasone alone (based on institutional experience and available literature) [7, 8, 9, 19]. For the study with a α of 0.1 and power of 80%, 50 patients will be needed to achieve the desired output. In the first stage, 22 patients will be needed for assessment and continue to stage 2 if > 10 responses are seen. Stage 2 of the study will be considered successful if > 29 responses are achieved using the pre‐specified response assessment criteria. Further considering an attrition rate of 10% from lack of follow‐up and another 10% for disease progression, an estimated 60 patients will be accrued in stratum A with the purpose of achieving 50 patients with endpoints available for analysis.

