Radionecrosis is mostly seen within the first 2 years, with the most common time being 6–18 months post‐radiation. Factors influencing the incidence and severity of RN include radiation dose (with higher rates > 60 Gy EQD2), radiotherapy technique, radiation volume, fractionation, and other biological factors, including intrinsic radiosensitivity [22, 23]. The diagnosis of radionecrosis can often be challenging due to the similar radiological appearance with disease recurrence, which should be ruled out as prognosis and treatment implications are completely different. The use of multiparametric imaging, including advanced functional sequences like perfusion‐weighted imaging and MR spectroscopy, can help differentiate radionecrosis from recurrence [24]. Typically, the changes appearing within the initial few months from radiation in the high‐dose region, the presence of Swiss cheese appearance on the T1‐contrast sequence, and hypointense to hypointense signal of T2‐weighted imaging should lead to suspicion for radionecrosis. Compared to recurrence, radionecrosis is typically hypoperfused on perfusion imaging and has a lower Choline: NAA peak on MR spectroscopy. Dynamic susceptibility contrast MRI has proven to be useful in differentiating radionecrosis from tumor recurrence, and standardized protocols have been recommended by consensus [25, 26]. Novel imaging techniques like treatment response assessment maps (TRAMs) which utilize multiple T1‐contrast sequences to explore differential washout of contrast from viable tumor and necrotic regions, or T1 mapping techniques can provide further clarity in differentiating radiation‐induced changes from disease recurrence [27, 28]. Amino acid PET with carbon‐11 methionine, DOPA, and FET can add to the MRI findings in improving the diagnostic performance in differentiating between radionecrosis and disease progression, with sensitivity and specificity of 80%–95%, as shown in different studies [29, 30, 31, 32, 33, 34]. In the current study, the patients will undergo multiparametric MRI, including spectroscopy, perfusion, and diffusion‐weighted imaging, to diagnose radionecrosis. In equivocal cases, additional imaging with FET or F‐DOPA will be considered for confirmation of the diagnosis. All the patients will be discussed in the multidisciplinary joint neuro‐oncology meeting before accrual in the study. The interval imaging after starting intervention (starting CHL) will be considered at 1 month with both MRI and PET for assessment of both morphological and functional response for primary endpoint assessment. Further imaging will be considered at 3 months for evaluation of long‐term response to CHL. Since there is always a possibility of inclusion of patients with progression, these patients will be excluded from analysis regarding the efficacy of CHL if recurrence is documented within 3 months from study accrual.

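### Section 2.9 allows only contingency-table tests for factors related to response, so continuous factors must be grouped and ordered factors lose their order (minor, secondary analysis)

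*Protocol article*

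**What the plan says.** Section 2.9 gives one sentence on factors and response: "The influence of patient, disease, and treatment‐related factors on the response (binary outcomes) will be analyzed using Pearson Chi‐square or Fisher's exact test as appropriate". The closing qualifier chooses between the two table tests and admits no third method. For survival, the same paragraph says "Univariate and multivariate analyses will be done using the log‐rank test and Cox regression, respectively". It reserves the t-test and ANOVA for the exploratory biomarkers. The threshold is a p-"value of < 0.05 will be considered statistically significant"; whether it is one- or two-sided is not stated.

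The factors are not listed in that section. Elsewhere in the article:

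- The Introduction reports steroid response rates of 25% to 60% and gives radiotherapy dose as one of the influences on them.
- The Discussion says "Factors influencing the incidence and severity of RN include radiation dose (with higher rates > 60 Gy EQD2), radiotherapy technique, radiation volume, fractionation". This concerns how often and how severely radionecrosis occurs, not response to treatment.
- Age and KPS appear as eligibility criteria, and KPS also as a repeated clinical assessment.
- IDH status is the one factor expressly named for a comparison of response to chlorophyllin (section 2.5). It is binary.

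**The concern.** The stated scope is broad (patient, disease and treatment factors), but the stated methods suit only categorical factors. Taken literally, the sentence means that a dose in Gy must be turned into groups before it can be related to response. The result then depends on where the cut falls, there is no effect estimate per unit of dose, and differences within a group are discarded. KPS is already scored in categories and needs no further cut, but a Pearson test on an r × 2 table ignores that the categories are ordered.

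This is a stated choice of method and not merely an omitted detail. The same paragraph names regression for survival and mean comparisons for biomarkers, and for response it names neither. With about 50 patients per stratum there is little information to give away. What is at stake is the chance of recognising a real determinant of response, which would be useful if the phase 3 work mentioned in the Discussion goes ahead.

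**Working it through.** **1. Inputs from the documents.** Stratum A: 50 evaluable patients ("with the purpose of achieving 50 patients with endpoints available for analysis") and a response rate that "is expected to be 65% as compared to the standard 50% response with the use of dexamethasone alone". Stratum B: 48 evaluable patients, 45% expected against 30%. Significance level 0.05, taken as two-sided.

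**2. The plan's own figures.** The article gives power only for the Simon designs. With X1 the stage 1 responses and X2 the stage 2 responses, success has probability P(X1 > r1 and X1 + X2 > r).

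- Stratum A (n1 = 22, r1 = 10, n = 50, r = 29): 0.0977 at a true rate of 50%, 0.8022 at 65%.
- Stratum B (n1 = 23, r1 = 6, n = 48, r = 18): 0.0963 at 30%, 0.8027 at 45%.

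These match Table 2 exactly. No power is stated for the factor analyses, so there is no figure of that kind to reproduce.

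**3. Assumptions for the factor analysis (not in the documents).** Factor X ~ N(0,1); logit P(response) = logit(p0) + log(OR)·X, with p0 = 0.65 (A) or 0.45 (B); OR is per SD. Two analyses were compared over 6,000 simulated trials per setting: the likelihood-ratio test from logistic regression on X, and the uncorrected Pearson chi-square after a median split.

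| OR per SD | A: continuous | A: median split | A: loss (points) | B: continuous | B: median split | B: loss (points) |
|---|---|---|---|---|---|---|
| 1.3 | 15.3% | 12.6% | 2.7 | 15.5% | 11.9% | 3.6 |
| 1.5 | 27.4% | 19.2% | 8.2 | 27.6% | 20.2% | 7.4 |
| 2.0 | 59.6% | 42.2% | 17.4 | 61.6% | 45.0% | 16.6 |
| 2.5 | 80.6% | 61.5% | 19.1 | 81.2% | 63.6% | 17.6 |
| 3.0 | 90.6% | 74.4% | 16.2 | 91.6% | 77.0% | 14.6 |
| 4.0 | 97.4% | 87.8% | 9.6 | 97.8% | 89.1% | 8.7 |

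Separate runs with other random draws agree to within about 2 points of loss; one put the loss at OR 1.5 as high as 9 points.

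**4. Is the gain bought with false positives?** At OR 1 the rejection rates were 6.1% (A) and 5.4% (B) for logistic regression, against 5.9% and 6.0% for chi-square. A t-test on the continuous factor rejected 5.2% and 4.7% at OR 1, and still had 57.8% and 59.1% power at OR 2. So the gain is not inflated error.

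**5. Other table analyses.** Over OR 1.3 to 4, Fisher's test on the median split loses about 8 to 33 points. Part of that is its own conservatism: it rejects 2.6% (A) and 3.0% (B) at OR 1. Chi-square with a cut at the 80th percentile loses about 5 to 44 points.

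**6. A different effect shape.** Suppose response jumps at a threshold and the cut is placed exactly there. For A, 80% against 50% averages (80 + 50)/2 = 65% over equal halves; for B, 60% against 30% averages (60 + 30)/2 = 45%. Power for chi-square against linear logistic regression is then about 61% to 62% against 44% in A, and 57% against 41% to 42% in B. Grouping wins by roughly 15 to 18 points.

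**The case against.** Four objections carry weight.

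- **The factors.** The plan does not list dose, volume, age or KPS as predictors of response to chlorophyllin, and nowhere says that it will dichotomise anything. The one factor it does name, IDH status, fits a table test. This stands for volume and age. For dose it stands only in part, because the Introduction does tie dose to steroid response rates.
- **The document type.** A factor list, coding and cut-points may sit in the full protocol or analysis plan, so their absence is no fault. This stands. The criticism is confined to the test that section 2.9 does fix.
- **The effect shape.** The Discussion describes dose by a threshold, and a step cut at its true location favours grouping. This stands as a limit on the size and even the sign of the loss. However, the threshold quoted is for the occurrence of radionecrosis. The article gives none for response and prespecifies no analysis cut.
- **Survival.** Cox regression is already planned for the multivariable model and can take continuous covariates. This stands: only the univariate log-rank step is affected, and no size was computed for it.

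A reader might infer that every factor loses a fixed 10 to 18 points of power. The documents do not support that, since they state no effect size, distribution or cut. The loss is under 4 points for a weak effect and can exceed 18 for others.

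**Conclusion.** The point holds in a limited form. As written, section 2.9 provides no method that uses the full scale of a continuous factor, or the order of an ordered one, when relating it to response. With a normal factor, a linear log-odds effect, two-sided 0.05 and the planned stratum sizes, a median split costs about 3 to 4 points of power at OR 1.3 per SD, 7 to 9 at 1.5 and 15 to 19 at 2 to 3. The simulation does not cover KPS, where only the ordering is lost.

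A reader might also conclude that the trial's efficacy result is weakened. It is not. The factor analysis is secondary, is not among the Table 1 endpoints and has no stated power. The go/no-go rule rests on counts of responders alone. The point is a minor one, worth correcting because the better method costs almost nothing.

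**What to change.** Amend section 2.9 along these lines:

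> Continuous or ordered factors will be related to response by logistic regression with the factor on its original scale, reported as an odds ratio per stated unit with a 95% confidence interval. The Pearson chi-square or Fisher's exact test will be used for categorical factors such as IDH status. In the univariate survival analysis, continuous factors will be examined by univariable Cox regression and categorical factors by the log-rank test.

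If the investigators believe that a factor acts through a threshold, they should state the cut and the reason for it before looking at the data.

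The cost is wording only: no further patients, visits or data, and SPSS 29, the package already specified, fits both models. The real downside is the assumption of a linear log-odds or log-hazard effect, which is hard to check with 48 to 50 patients per stratum and should be acknowledged when results are reported.

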
The most commonly used medication for RN is corticosteroids, which can relieve symptoms and lead to reversal or stability of radiological findings in a proportion of patients. There are no guidelines regarding the dose and duration of use of corticosteroids and also the type of steroids (with dexamethasone preferred by the majority). Typically, in symptomatic patients, at least a few weeks of steroid treatment are required for optimal clinical benefit. There are concerns about certain adverse effects both with short‐and long‐term use of steroids, including insomnia, acute psychosis, hyperglycemia, osteoporosis, risk of infections, skin changes, myopathy, and adrenocortical insufficiency, which can itself lead to new complications affecting quality of life. Also, some patients often turn into a state of steroid dependence with relapse of symptoms upon withdrawal of steroids. In refractory cases, the anti‐angiogenic agent bevacizumab can provide significant benefit; however, the major challenges remain the need for frequent hospital visits for intravenous administration (typically delivered every 2–3 weeks), associated costs, and side effects including hypertension or life‐threatening hemorrhages. Some agents with questionable benefits include edaravone, pentoxifylline, and hyperbaric oxygen therapy [8, 35]. The current study will use CHL to treat radionecrosis, which has demonstrated anti‐inflammatory and antioxidant properties with a free radical scavenging effect in preclinical studies, with the pathophysiology of radionecrosis being considered a pro‐inflammatory environment [15, 36]. In the study, we are considering patients with symptomatic and asymptomatic radionecrosis in two different strata since the burden of necrosis, tempo of disease, and clinical outcomes are expected to be different. In the symptomatic stratum, patients will be treated with CHL in addition to oral dexamethasone, which is otherwise used as the standard first‐line therapy for symptomatic RN in our institution, while in the other stratum (asymptomatic), patients will receive CHL alone to explore the role of CHL as a steroid‐sparing agent.

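### Section 2.9 tests response factors with chi-square or Fisher's exact test and does not mention strata A and B, which the design expects to differ by 20 points in response

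*Protocol article*

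**What the plan says.** The protocol article, section 2.9 (Statistical Analysis), states that the influence of patient, disease and treatment characteristics as "factors on the response (binary outcomes) will be analyzed using Pearson" chi-square or Fisher's exact test. For survival, "Univariate and multivariate analyses will be done using the log‐rank test and Cox regression, respectively". A p-value below 0.05 "will be considered statistically significant". The section does not mention the strata, and no multivariable method is named for response.

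Elsewhere the article treats the strata as different populations:

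- Section 2.7: the 1-month response in stratum A "is expected to be 65% as compared to the standard 50% response with the use of dexamethasone alone".
- Section 2.8: in stratum B, "approximately 30% of patients continue to be neurologically/radiologically stable or show regression of imaging findings" with no further intervention, and with the study drug "45% of patients are assumed to remain clinically and neurologically stable".
- Section 2.4: a one-month dexamethasone taper is planned in stratum A, and no steroid in stratum B.
- Section 2.5: steroid failure at 1 month means an increase over the planned taper in A, but any dexamethasone requirement in B. The same section says that the IDH subgroup analysis of response covers both strata.
- Section 3 (Discussion): two strata are used "since the burden of necrosis, tempo of disease, and clinical outcomes are expected to be different".

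**The concern.** By the article's own assumptions, stratum is a strong determinant of response. Neither a Pearson chi-square nor a Fisher test on a single two-by-two table can carry a stratum term. If the table pools A and B, a characteristic commoner in one stratum picks up part of the 20-point gap and can seem to predict response when it only marks stratum membership. The pooled table would also combine two definitions of steroid failure.

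Such characteristics are plausible. Strata are defined by new or worsening deficits, and the Discussion expects the burden of necrosis to differ between them. Planned steroid use is the limiting case, because it coincides with stratum.

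At stake is the credibility of any reported predictor of response. Because the text allows both a pooled and a within-stratum analysis, the choice could also be made after the data are seen.

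**Working it through.** **Inputs from the article.** Evaluable patients: 50 in A and 48 in B (sections 2.7 and 2.8). Expected response: 65% and 45%. Null response: 50% and 30%. The gap is 65 − 45 = 20 points, or 50 − 30 = 20 points. Significance level: 0.05 (section 2.9).

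**Assumption not in the article.** The prevalence of the factor in each stratum, varied from 50/50 to 90/10 (percent in A / percent in B).

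**Step 1: reproduce the article's own figures.** For a two-stage design with first-stage size n1, first-stage limit r1, total size n and final limit r, the chance of declaring success at response rate p is P(X1 > r1 and X1 + X2 > r), with X1 ~ Bin(n1, p) and X2 ~ Bin(n − n1, p).

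- Stratum A (n1 = 22, r1 = 10, n = 50, r = 29): 0.0977 at p = 0.50 and 0.8022 at p = 0.65.
- Stratum B (n1 = 23, r1 = 6, n = 48, r = 18): 0.0963 at p = 0.30 and 0.8027 at p = 0.45.

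All four agree with Table 2. These rules are applied within each stratum, so the present point does not touch them.

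**Step 2: apparent effect of a factor with no true effect.** On pooled data,

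apparent difference = (response in A − response in B) × (share of A among patients with the factor − share of A among patients without it).

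At 70/30, patients with the factor number 50 × 0.7 = 35 in A and 48 × 0.3 = 14.4 in B, so the share of A is 35/49.4 = 0.708. Patients without it number 15 in A and 33.6 in B, so the share of A is 15/48.6 = 0.309. The apparent difference is 0.20 × (0.708 − 0.309) = 0.080, or 8 points (59.2% against 51.2%). The same arithmetic gives 4 points at 60/40, 12 at 80/20 and 16 at 90/10.

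**Step 3: how often that is significant.** 200,000 simulated trials per setting: the factor is drawn with the assumed prevalence in each stratum, and response is drawn from the stratum rate alone. Each trial is tested at 0.05 by a pooled Pearson chi-square and by a Cochran-Mantel-Haenszel (CMH) test stratified by A/B.

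| Prevalence A/B | Pooled, 65% vs 45% | Pooled, 50% vs 30% | CMH, both settings |
|---|---|---|---|
| 50/50 | 5.2% | 5.2% | 5.0% |
| 55/45 | 5.7% | 5.6% | 4.9–5.0% |
| 60/40 | 7.1% | 7.1% | 4.9–5.0% |
| 70/30 | 13.0% | 13.0% | 4.9% |
| 80/20 | 22.9% | 23.2% | 4.8–4.9% |
| 90/10 | 36.7% | 37.2% | 4.8–4.9% |

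**Step 4: the limiting case.** A factor identical to stratum (100/0) is significant in 53.5% of pooled trials at the expected rates and 52.7% at the null rates. The CMH test never rejects here, because the factor does not vary within a stratum. Stratifying therefore cannot estimate the effect of planned steroid use. It only prevents that effect from being reported as if it could be separated from stratum.

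**Survival.** The article gives no progression-free or overall survival assumption by stratum, so no corresponding calculation is possible for the log-rank or Cox analyses.

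**The case against.** The strongest reply is that pooling is nowhere stated. Every test named can be run within a stratum, which removes the confounding. Each stratum has its own null rate, target and decision rules, and the one factor analysis described separately, by IDH status, covers both strata. A condensed article may also leave such detail to a fuller protocol or analysis plan. This stands in part: a reader might infer that the plan commits to pooled tests, and the text does not support that. But section 2.9 does fix the test family for response. It names no adjusted method, and it does not repeat for other factors the reference to both strata that the IDH analysis carries. The within-stratum reading is possible but not stated.

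Four further limits stand:

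- A reader might infer that any factor linked to symptoms would look predictive. The figures do not show that. A weak link (55/45 or 60/40) gives 6% to 7%, and even stratum itself is flagged in only about 53% of trials.
- A reader might extend the 20-point gap to survival. It concerns response only, and the Cox model lists no covariates, so stratum may be among them.
- A reader might assume that these analyses will select patients for a later trial. The Discussion ties phase 3 planning to usefulness and the primary endpoint, and mentions prediction of response only for exploratory blood markers.
- The analyses are not the confirmatory test of either stratum.

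**Conclusion.** The point holds for the response-factor analyses, on the condition that the strata are pooled. Section 2.9 neither states nor excludes pooling. On that condition the false-positive rate rises from 5% to about 7%, 13%, 23% or 37% as the assumed prevalence goes from 60/40 to 90/10, with almost the same figures at the expected and the null response rates. The calculation rests on the planned 50 and 48 evaluable patients, on both strata running to full size, and on a factor with no effect within either stratum.

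For survival, only the missing statement about strata can be noted, with no size attached. The change is worth making because it is cheap and prevents spurious predictors, but no primary conclusion depends on it.

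**What to change.** Amend section 2.9 to state that:

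1. factors influencing response are tested with a Cochran-Mantel-Haenszel test or a logistic regression with stratum as a term, or are reported within each stratum;
2. the log-rank test and the Cox model are stratified by A/B, and Kaplan-Meier curves are shown by stratum;
3. planned steroid use is not assessed as a factor, because it coincides with stratum.

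The cost is a few sentences. No new data, no change in sample size and no change to the decision rules are needed, and standard software runs all of these methods.

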### Response Evaluation

2.5

The study endpoints have been summarized in Table 1. Response to CHL will be considered as the absence of all three criteria as follows:
Imaging progression of radionecrosis: Defined as an increase in T1‐contrast or T2w hyperintensity of the index lesion on the MRI brain, as assessed by a neuroradiologist. The PET scan at 1 month will be assessed by the nuclear medicine physician, and findings will be interpreted based on the avidity of the index lesion.Clinical deterioration will be considered as a ≥ 2‐point drop in the NPS at assessment points (1 and 3 months) from baseline NPS.Dexamethasone requirement: Any increase in the dexamethasone requirement during the predetermined tapering schedule will be considered refractory RN for stratum A. Any requirement of dexamethasone after CHL will be considered a failure of CHL in stratum B. Similarly, after the 1st month (when no dexamethasone use is planned in stratum A), the use of dexamethasone will be considered a failure of CHL for stratum A during the analysis of response at the 3rd month.

**TABLE 1 cam470657-tbl-0001:** Objectives and endpoints of CHROME study.

Study objective	To assess the efficacy of oral CHL in the treatment of radionecrosis in patients with diffuse glioma
Study endpoints	
Primary endpoint	Response rates (clinical‐radiological) at 1 month with the use of CHL
Secondary endpoint	Clinical‐radiological response rates at 3 months Biological response rates using functional imaging (PET and MRI) Survival analysis (Progression‐free survival and overall survival) EORTC QOL C‐30 and BN‐20 questionnaire at baseline, 1‐month, and at 3‐month follow‐ups NANO scale score QTWIST score
Exploratory endpoint	Temporal changes of inflammatory and tumor‐related biomarkers obtained from the serum

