Therefore, for study analysis, combined evaluation (radiological, clinical, steroid requirement) will serve as a method of testing the efficacy of CHL, with progression in any single domain of the above three considered a failure, as mentioned above. Patients with unequivocal disease progression on imaging at 1 or 3 months will be excluded from RN response assessment (since the possibility of recurrence component is likely to contribute to neurological functioning and outcomes). Any discrepancies or equivocal findings will be discussed in a joint neuro‐oncology meeting (JNOM) for a consensus decision. No additional follow‐up visits will be required as per study protocol since patients with RN are called at 1 month for clinical evaluation and at 3 months for radiological and clinical evaluation. However, additional imaging will be undertaken with MRI and PET scan at 1 month after starting CHL. Imaging with MRI brain tumor protocol will be done at 3 months as the standard of care following institutional practice. The study workflow has been presented in Figure 2. A subgroup analysis of response to chlorophyllin will be done for patients with IDH‐mutant and IDH‐wild gliomas for both strata. As a part of the study (exploratory endpoint), 12–15 mL blood samples (EDTA and plain tubes) will be collected at baseline, 1 month, and 3 months. The blood will be analyzed for inflammatory indices from routine hemogram serum biochemistry, including albumin, CRP, and ferritin, along with additional exploratory markers like cytokines, chemokines (GM‐CSF, IFN‐gamma, TNF‐beta, interleukins, etc.), oxidative stress markers, proteomics, and metabolomics.

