The primary endpoint used in the study includes combined clinical and radiological criteria at 1 month for assessment of response. Other endpoints include 3‐month response and additional patient‐reported outcomes, survival outcomes, toxicity, and exploratory analysis for blood markers, which can predict the response to treatment. If proven useful and the primary endpoint is met, further phase 3 randomized studies will be planned to determine the efficacy of CHL in the treatment of radionecrosis. If proven useful, this will open a new avenue for the treatment of radionecrosis as a well‐tolerated oral therapy, avoiding or reducing the side effects of current standard treatment with corticosteroids.

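### A single unadjusted p<0.05 rule also covers the exploratory cytokine, proteomic and metabolomic panels; false discovery rate control would serve better, and the within-patient analysis should be named

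*Protocol article*

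**What the plan says.** The method is in Section 2.9 (Statistical Analysis) of the protocol article: "For exploratory analysis, the biomarkers will be compared using the" t-"test and ANOVA, as appropriate". The next sentence sets the threshold for the whole section, a p-value "of < 0.05 will be considered statistically significant". No exception or adjustment is given for the biomarkers.

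Section 2.5 (Response Evaluation) describes what is measured. Blood samples "will be collected at baseline, 1 month, and 3 months". The analytes run from routine inflammatory indices through cytokines and chemokines to "oxidative stress markers, proteomics, and metabolomics". Their number is not stated.

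Two uses of the markers appear. Table 1 gives the exploratory endpoint as "Temporal changes of inflammatory and" tumor-related serum markers, which is change within patients. The Discussion (Section 3) speaks of "exploratory analysis for blood markers, which can predict the response to treatment", which is a comparison between patients.

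**The concern.** A 5% rule per test suits a handful of planned comparisons. Applied marker by marker to proteomic and metabolomic panels, it yields a list of significant markers even when nothing has changed, and the list grows with the size of the panel. Since the markers are meant to help predict response, chance findings could be carried into later work, including the phase 3 trials that the Discussion envisages.

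A second, smaller issue is that the endpoint is change across three samples from the same patient, yet the text does not say whether the t-test is paired or the ANOVA is for repeated measures. If independent-group versions were applied across visits, real changes could be missed.

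**Working it through.** The article gives no sample size, power or error rate for the biomarkers, so there is no figure of its own to reproduce.

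**Inputs from the article:** threshold 0.05 (Section 2.9); three sampling times (Section 2.5); 50 evaluable patients planned in stratum A (Section 2.7).

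**Assumptions:** number of analytes m from 10 to 1,000; two-sided tests; within-patient correlation ρ of 0.3, 0.5 or 0.7.

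**1. False positives when the tests hold their level.** This covers paired or repeated-measures tests across visits, and ordinary independent-group tests of responders against non-responders. With m markers and no true effects:

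- expected false positives = 0.05 × m
- chance of at least one, if the markers are independent = 1 − 0.95^m

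| m (assumed) | Expected per comparison | Chance of at least one | Expected over three pairwise visit contrasts (0.15 × m) |
|---|---|---|---|
| 10 | 0.5 | 0.40 | 1.5 |
| 100 | 5 | 0.994 | 15 |
| 1,000 | 50 | about 1 | 150 |

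The expected counts do not depend on independence between markers. The chance of at least one does. It is shown for one comparison per marker.

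**2. What would follow if unpaired tests were run across visits.** For equal variances, the unpaired standard error of a change exceeds the true one by the factor 1/√(1−ρ). At ρ = 0.5 this is 1/√0.5 = 1.41, or 41% too large. The critical value of 1.96 on the unpaired scale then corresponds to 1.96/√(1−ρ) true standard errors. A correctly paired test with 80% power has an expected statistic of 1.96 + 0.84 = 2.80. Hence:

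- power when unpaired = Φ(2.80 − 1.96/√(1−ρ))
- two-sided type I error when unpaired = 2Φ(−1.96/√(1−ρ))

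| ρ (assumed) | 1.96/√(1−ρ) | Power (80% if paired) | Type I error |
|---|---|---|---|
| 0.3 | 2.34 | Φ(0.46) = 68% | 0.019 |
| 0.5 | 2.77 | Φ(0.03) = 51% | 0.006 |
| 0.7 | 3.58 | Φ(−0.78) = 22% | 0.0003 |

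A simulation (20,000 runs, n = 50, normal data) agrees. Unpaired type I error was 0.021, 0.006 and 0.0004 at the three correlations, against about 0.05 for the paired test. For a shift of 0.3 standard deviations, power unpaired against paired was 0.29 against 0.43, 0.26 against 0.54, and 0.20 against 0.76.

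**3. The two effects are alternatives.** With positive correlation, unpaired tests across visits are conservative. At ρ = 0.5, 1,000 null markers would give about 1,000 × 0.006 = 6 false positives, not 50. The counts in step 1 therefore apply to correctly formed tests, and the power loss in step 2 to wrongly formed ones. A single test cannot suffer both.

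**The case against.** The strongest objection is that the analysis is labelled exploratory, that it plays no part in the success rules (which rest on response counts in Sections 2.7 and 2.8), and that a condensed article commonly leaves test form and multiplicity for omics data to the full protocol or SAP, neither of which is shown. This stands as a limit on severity. It also disposes of any complaint that details are merely absent. It does not remove the multiplicity point, because the article is not silent: it names the tests and states one significance rule for the section.

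A reader might infer that the plan ignores pairing. The text does not support this. A paired t-test is a t-test, a repeated-measures ANOVA is an ANOVA, and the words "test and ANOVA, as appropriate" leave the choice open. Independent-group tests are also legitimate for comparing responders with non-responders.

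A reader might also infer that many false discoveries are guaranteed. They are not: the number of analytes is not given, and 10 null markers would yield 0.5 on average.

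Nor does the article say that patients with a missing sample will be dropped, or that the markers are skewed. Neither is part of this point.

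**Conclusion.** The point holds as a minor one. Followed as written, Section 2.9 would declare about 5% of null markers significant in each comparison. This is true both for correctly paired tests of change and for valid between-group tests. For an omics panel of 100 to 1,000 analytes (assumed) that means 5 to 50 chance findings per comparison if no marker truly changes, and three times as many if all three visit pairs are tested.

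On pairing, the most that can be said is that the form of the test is left open for an endpoint that is by definition within-patient. The fall in power from 80% to about 51% is conditional on unpaired tests across visits and on an assumed correlation of 0.5. It is not a consequence of what the article states.

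The primary endpoint and the stage 1 and final decision rules are untouched.

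**What to change.** In Section 2.9, or in the SAP with a matching sentence here:

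- **Panels.** For the cytokine, proteomic and metabolomic panels, replace p<0.05 with declaration by the Benjamini-Hochberg false discovery rate, for example at 10%. State the set of tests over which it is applied, including visit contrasts, and report the number of analytes tested.
- **Change over time.** Name a within-patient analysis, for example a linear mixed model with visit, stratum and visit-by-stratum terms and a patient random effect, using all available samples. The interaction matters because Section 2.4 gives stratum A a month of tapering dexamethasone and stratum B no steroids, so the inflammatory markers may follow different courses.
- **Prediction of response.** Keep independent-group tests for responders against non-responders, under the same false discovery rule for the panels.

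The cost is a few sentences and fewer markers called significant. No patients, samples or visits are added, and the primary decision does not change.
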